#### Secondary Outcome Measure

The secondary outcome of this study will be the change in the mental health literacy score. This is defined by a change in the total score on the Mental Health Literacy Questionnaire (MHLQ) between the baseline and follow-up assessments at weeks 5 and 12 (Table 1).

**Table 1 table1:** Overview of measurements.

Instrument	Aim	Time of measurement		
		T_0_ (Baseline)	T_1_ (Posttest at week 5)	T_2_ (Follow-up at week 12)
Sociodemographics	Characteristics of participant	Yes		
PHQ-9	Symptoms of depression	Yes	Yes	Yes
GAD-7	Symptoms of anxiety	Yes	Yes	Yes
MHLQ	Mental health literacy	Yes	Yes	Yes

### Instruments

#### Patient Health Questionnaire 9

The PHQ-9 is used to measure the severity of depression based on the *Diagnostic and Statistical Manual of Mental Disorders* (Fourth Edition; *DSM-IV*) criteria. It consists of nine items, each item rated on a scale from 0 to 3, and a total score range from 0 to 27. Both the validated English [24] and Malay [25] versions of the questionnaire are used in this study.

#### Generalized Anxiety Disorder 7

The GAD-7 is used to measure the severity of anxiety based on the *DSM-IV* criteria. The seven items are each scored from 0 to 3, with an overall range score of 0 to 21. Both the validated English [26] and Malay [27] versions of the questionnaire are used in the study.

#### Mental Health Literacy Questionnaire

Some studies uses case vignettes to measure the knowledge of participants on mental health illness, such as depression, anxiety, and schizophrenia. However, the education level of a community in a developing country such as Malaysia is lower compared to developed countries. Because of this, we are unable to use case vignettes and specific facts to assess the mental health knowledge of the participants. Therefore, we had to create items measuring knowledge based on a local context, taking into account cultural-specific issues.

To assess the knowledge on depression and anxiety, eight items were developed based on the content of the psychoeducational intervention program (general knowledge on mental health). Another four items were adapted from the MHLQ from the domain of knowledge and capability [28] and were modified based on the suitability of the items measuring depression and anxiety in this study. In total, 12 items were used to assess the participant’s knowledge on depression and anxiety. The items are coded as yes and no. The items will be summed, with a total score ranging from 0 to 12. Both English and Malay versions of the questionnaire are used in this study.

### Sample Size

The sample size for this study was calculated using a formula by Lemeshow et al [29]: n=(2σ^2^[Z_1−α/2_+Z_1−β_]^2^)/([μ_1_−μ_2_]^2^).

Using a power of 80%, a confidence interval of 95%, a pooled standard deviation of 9.865, and a baseline and posttest mean score of 21.1 and 16.2, respectively, in the intervention group [11], the calculated sample size was estimated to be 64 participants. Taking into consideration a 30% dropout rate [30], the final sample size calculated was 84 participants in each group.

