### Inclusion and Exclusion Criteria

Participants who participated in the first phase of this study will be invited to participate in this study. The inclusion criteria of this study are: (1) participants who have participated in the first phase of this study and who are still living in Selangor, (2) have access to a computer and have an Internet connection, and (3) are Internet-literate. Potential participants will be excluded if they are currently receiving any psychotherapy for diagnosed psychiatric disorders.

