## Discussion

This RCT study protocol is aimed to investigate the effectiveness of a Web-based psychoeducational intervention for depressive and anxiety symptoms for the adult community in Selangor, Malaysia. Self-management through the Internet offers the opportunity to reach and treat the community who may suffer from mild-to-moderate depression and anxiety, and for those who are reluctant to seek for assistance from medical professionals. In addition, it can serve as an appealing modality for quick help to manage these problems. Web-based programs can provide the advantage of disclosing certain information better than face-to-face interviews. Moreover, information can be accessed 24/7 and is available to a wider community. This can be very useful when an immediate need is required for information on management.

To our knowledge, Internet-based management for both depression and anxiety in the community has not been studied in Malaysia. This study could give an insight on the effectiveness and applicability of a Web-based psychoeducation program in the current population. The strength of this study is that the psychoeducational intervention program is developed based on the predictors of depression [22] and anxiety in our own population. The program aims to address the predictors that contribute to depression and anxiety in our community. This brief Web-based program will enable the community to use easy, user-friendly, valid, and reliable tools for assessing their mental health status.

Second, the availability of the program in both English and Malay languages is an additional plus point. Participants can choose their preference language to complete the sessions. Third, the assessments are available in both languages and have been validated in our population. Fourth, the intervention program was designed to be as brief as possible to increase the acceptability of the program versus other lengthier interventions, which could further increase the dropout rates.

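### The sample-size inputs are impossible on the GAD-7 and implausible on the PHQ-9, so the stated 80% power is not established for either primary outcome

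*Protocol article*

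**What the plan says.** The Sample Size section uses the standard formula for comparing two independent means, with 80% power and a two-sided 5% level. Its inputs are "a pooled standard deviation of 9.865, and a baseline and posttest mean score of 21.1 and 16.2". The section attributes these means to the intervention group of a cited study and does not say which questionnaire produced them. The Introduction describes that study as a comparison of two Internet interventions and mentions only depressive symptoms. The result is 64 per group, raised to 84 for 30% dropout. No second calculation is given.

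The Primary Outcome Measure section names change in both the PHQ-9 and the GAD-7. The Instruments section fixes their ranges. For the PHQ-9: "each item rated on a scale from 0 to 3, and a total score range from 0 to 27". For the GAD-7: "The seven items are each scored from 0 to 3, with an overall range score of 0 to 21".

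Entry does not depend on symptom level. The inclusion criteria ask for "participants who have participated in the first phase of this study and who are still living in Selangor", plus Internet access and Internet literacy. People now receiving psychotherapy for a diagnosed psychiatric disorder are excluded. The Discussion says that Internet self-management can "treat the community who may suffer from mild-to-moderate depression and anxiety".

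**The concern.** A power statement has to refer to the outcome that will be tested. Here there are two primary outcomes and one set of planning values, and those values do not fit within the range of one of the two scales. On the other scale they describe a group with very high and very dispersed scores, whereas recruitment is from a household survey with no symptom cut-off.

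The difference entered in the formula is also of the wrong kind. The formula needs a difference between two groups. The 4.9 points are a change over time within one treated arm, which includes whatever improvement would have occurred without treatment.

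What is at stake is how a null result is read. Someone who takes the section at face value would conclude that the trial had 80% power for a 4.9-point difference on its own scales with an SD near 10. Neither number has been shown to apply to the PHQ-9, and they cannot apply to the GAD-7.

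**Working it through.** **Inputs.** From Sample Size: SD 9.865, means 21.1 and 16.2, 80% power, two-sided 5%, 64 before and 84 after dropout. From Instruments: PHQ-9 0 to 27, GAD-7 0 to 21. The sum of the normal quantiles is 1.960 + 0.842 = 2.802.

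**1. The plan's own figure.** Difference 21.1 − 16.2 = 4.9; ratio 4.9/9.865 = 0.497. Then n = 2 × (9.865 × 2.802 / 4.9)² = 63.63, rounded up to 64. The figure reproduces. The stated 84 is 64 × 1.3.

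**2. Do the inputs fit the GAD-7?** The mean does not, because 21.1 > 21. The SD can be checked separately: a score confined to 0 to M with mean m has an SD of at most √(m(M − m)). At m = 16.2 and M = 21 this is √(16.2 × 4.8) = 8.82, which is below 9.865.

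**3. Do they fit the PHQ-9?** Mathematically, yes.
- At mean 21.1 the largest SD is √(21.1 × 5.9) = 11.16.
- At mean 16.2 it is √(16.2 × 10.8) = 13.23.
- But 21.1/27 = 78% of the maximum score, and the ceiling is only (27 − 21.1)/9.865 = 0.60 SD above the mean.
- The variance is 9.865²/(21.1 × 5.9) = 78% of the largest possible. As an illustration, the maximum-entropy distribution on 0 to 27 with this mean and SD puts about 69% of people at 25 to 27 and about 16% at 0 to 2.

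That is not a credible picture of a community sample without a symptom threshold.

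**4. Floor.** Neither scale goes below 0, so a 4.9-point between-arm benefit needs a control mean of at least 4.9. For assumed control means of 3 or 4, subtracting 4.9 gives −1.9 or −0.9. For assumed means of 5 to 8 it leaves 0.1 to 3.1. The document gives no PHQ-9 or GAD-7 mean to choose between these.

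**5. What the sample size supports.** Detectable difference in SD units = 2.802 × √(2/n).
- n = 64: 0.495.
- n = 58 (84 × 0.7 = 58.8): 0.520.

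In points at n = 64, for assumed SDs of 3, 4, 5 and 6: 1.49, 1.98, 2.48 and 2.97. On those SDs, 4.9 points would be between 4.9/6 = 0.8 SD and 4.9/3 = 1.6 SD.

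**6. Sensitivity.** Number needed per arm for 80% power at between-arm differences of 1, 2 and 3 points (all assumed):
- SD 4: 252, 63, 28.
- SD 5: 393, 99, 44.
- SD 6: 566, 142, 63.

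With 64 analysed per arm, power over this grid runs from 15.5% (SD 6, 1 point) to 98.9% (SD 4, 3 points). No single corrected N follows from the document.

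**The case against.** The best defence is that the formula uses only the ratio 0.497, which has no units. On that view the scale of the cited study is irrelevant, 64 per arm gives 80% power for a half-SD difference on any scale, and the section never calls 4.9 points a PHQ-9 or GAD-7 target. Much of this stands: the arithmetic is correct and N need not change. It does not rescue the power claim, because the section does not present its inputs as a standardised effect. The ratio also comes from change within one arm, so it gives no support for a half-SD difference between arms on either outcome.

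Nor can it be put down to condensation in an article. The inputs are printed, and they conflict with score ranges printed in the same Methods section.

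Three stronger readings are tempting and go too far.
- A reader might infer that the values cannot have come from either instrument and must belong to a wider scale. That is shown only for the GAD-7; on the PHQ-9 they are extreme but possible.
- A reader might infer that the values cannot fit an unselected sample. The document gives no phase 1 score distribution, so implausible is as far as the evidence goes.
- A reader might want a treatment-by-baseline interaction and a claim limited to symptomatic participants. Such terms are commonly left to an analysis plan, the stated objective concerns the community, and the Results section says that data collection was already complete, so the term could not be truly pre-specified.

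**Conclusion.** The point holds and should be fixed. The only stated basis for 80% power is impossible for the GAD-7 on both mean and SD, so the anxiety outcome has no applicable calculation. For the PHQ-9 the basis is possible but implausible, and it rests on a within-arm change used as a between-arm difference. Power is therefore not established for either primary outcome. That does not make 64 or 84 per arm too small; whether it is depends on SDs and effects that the document does not give.

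The GAD-7 result needs no assumption beyond the printed range; the limit of 8.82 treats 9.865 as an SD at the posttest mean, but the baseline mean fails regardless. The PHQ-9 judgement rests on the absence of a symptom threshold. The range of 1.5 to 3.0 points rests on an assumed SD of 3 to 6 and on a simple comparison of two means.

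**What to change.** In the Sample Size section:
- State that the two means and the SD are carried over from the cited study, name the scale they were measured on, and say that they are not a target on the PHQ-9 or GAD-7.
- Replace them with the detectable between-arm difference for each primary outcome at 80% power: about 0.50 SD with 64 analysed per arm, and about 0.52 SD with 58 per arm if 30% of 84 are lost.
- Convert each to points with the PHQ-9 and GAD-7 SDs from the phase 1 survey or from baseline data pooled over arms, and give the SDs used.

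This is a change of wording using data that the investigators should already hold. N does not change, and since data collection is complete it could not. The cost is a less favourable power statement that shows its assumptions, and a conversion to points that is made after the design was fixed and should be labelled so.

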A study by Mackinnon and colleagues [17] comparing the outcome of CBT and a depression information website showed a reduction in depressive symptoms in both intervention groups compared to the control group. The study also found that the effect persisted at 12 months of follow-up.

A study comparing the effectiveness of two Internet interventions found that both CBT and psychoeducation reduce depressive symptoms in the intervention group as compared to the control group [11]. The information site for depression was also found to improve the participants’ knowledge on their medical, psychological, and preference of lifestyle treatments.

Due to the importance and significance of self-management to reduce depression and anxiety, we aim to investigate the effectiveness of a 4-week Web-based psychoeducational intervention program for depressive and anxiety symptoms in the community of Selangor, Malaysia. As far as we know, there is currently no available published data on Internet-based management in Malaysia on these disorders. Therefore, this study was designed to evaluate the effectiveness and applicability of a Web-based psychoeducational intervention program in our population.

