## Methods

### Study Design

A two-arm parallel randomized controlled trial (RCT) of a single-blind study will be conducted to compare 4 weeks of a Web-based psychoeducational intervention program versus a waitlist control group. This study (phase 2) is a continuation of a preliminary study (phase 1), which consisted of a cross-sectional survey to detect depression and anxiety among adults in community households in the state of Selangor, Malaysia. Selangor is one of the 13 states in Malaysia, with the highest level of urbanization. In the previous study, the cross-sectional study was conducted in three of nine districts in Selangor, namely Hulu Langat, Klang, and Sepang. The study population of this study is only representative of Selangor.

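### The sample size enters a within-arm pre-to-post change as the between-group difference, so the stated 80% power is not established for the intervention-versus-waitlist comparison

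*Protocol article*

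**What the plan says.** The Sample Size section gives n = 2σ²(Z₁₋α/₂ + Z₁₋β)²/(μ₁ − μ₂)². The inputs are "Using a power of 80%, a confidence interval of 95%, a pooled standard deviation of 9.865", and for the means "a baseline and posttest mean score of 21.1 and 16.2, respectively, in the intervention group [11"]. The result is that "the calculated sample size was estimated to be 64 participants", and then: "Taking into consideration a 30% dropout rate [30], the final sample size calculated was 84 participants in each group". The 64 reads as per group, because it is inflated to 84 in each group.

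Under Study Design, the purpose is to "compare 4 weeks of a Web-based psychoeducational intervention program versus a waitlist control group". Under Primary Outcome Measure, the outcome is change in PHQ-9 and GAD-7 from baseline to weeks 5 and 12. Under Statistical Analysis, the two groups are compared over the three time points by mixed between-within ANOVA.

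On the source of the 4.9, the Introduction says only that "both CBT and psychoeducation reduce depressive symptoms in the intervention group as compared to the control group [11"]. It gives no control-arm mean, control-arm change or net difference.

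**The concern.** The factor 2σ² belongs to a comparison of two independent groups, so μ₁ − μ₂ should be the difference expected between the arms. Here it is the fall from baseline to posttest within one arm. The two quantities coincide only if controls do not change.

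In a waitlist trial with repeated self-rated symptom scores, some control improvement is plausible, for example through regression to the mean or natural recovery. Each point of it comes off the 4.9. Nowhere does the article say that zero control change is assumed, or why.

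At stake is how the result is read. This paragraph is the only justification given for the trial's size. A null result set against a stated 80% power would be taken as evidence from an adequately powered trial, when the calculation does not show that.

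**Working it through.** **Inputs (Sample Size section).** Power 80%; two-sided α = 0.05 (95% confidence, Z at 1 − α/2); σ = 9.865; means 21.1 and 16.2, so μ₁ − μ₂ = 4.9; standardised, 4.9/9.865 = 0.497.

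**Step 1: reproduce the 64.** n = 2 × 9.865² × (1.960 + 0.842)²/4.9² = 63.63, rounded up to 64 per group. This matches. A one-sided version gives 51. A paired version, n = σ_change²(Z + Z)²/4.9² with σ_change = 9.865√(2(1 − ρ)), gives 45, 32 and 20 for assumed correlations ρ of 0.3, 0.5 and 0.7. None of these is 64. The 4.9 was therefore used as a difference between two independent groups.

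**Step 2: what the trial's comparison needs.** The relevant effect is intervention change minus control change, that is 4.9 − c, where c is the control improvement. The article gives no value for c, so no single corrected sample size can be computed. The values of c below are assumptions.

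**Step 3: illustrate.** Power ≈ Φ((4.9 − c)/(9.865√(2/n)) − 1.960), with 9.865√(2/64) = 1.744 and 9.865√(2/84) = 1.522. For example, c = 1 and n = 64 gives 3.9/1.744 − 1.960 = 0.276, and Φ(0.276) = 0.61.

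| Assumed c (points) | Net difference | Power, 64 analysed per arm | Power, all 84 analysed per arm | n per arm for 80% |
|---|---|---|---|---|
| 0 | 4.9 | 80% | 90% | 64 |
| 0.5 | 4.4 | 71% | 82% | 79 |
| 1 | 3.9 | 61% | 73% | 101 |
| 2 | 2.9 | 38% | 48% | 182 |

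**Step 4: sensitivity to the analysis.** The article does not say whether 9.865 is an SD of scores or of changes. If it is an SD of scores, a change-score comparison has SD 9.865√(2(1 − ρ)):

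- ρ = 0.7: SD 7.641. With 64 per arm, power is 82% at c = 1 and 57% at c = 2.
- ρ = 0.5: SD 9.865, so the table above is unchanged.
- ρ = 0.3: SD 11.672. With 64 per arm, power is 66% even at c = 0.

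The correlation is not given, so it cannot be said which way the analysis moves the figures.

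**The case against.** The strongest reply is that the control change is unknown, so no power loss has been demonstrated. If controls did not change, 4.9 would be the between-group difference, and a repeated-measures analysis may gain precision that the simple formula ignores. This stands as far as it goes. The table is illustrative, its range for c has no source in the article, and the 82% at ρ = 0.7 and c = 1 shows that 80% can survive some control improvement. But the article claims no such gain, a low correlation works the other way, and a different variance does not turn a within-arm change into a between-arm effect.

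A reader might infer that the trial has 80% power only if controls show zero change. The documents do not support that. With all 84 per arm analysed, power is 82% at a 0.5-point control change. With ρ = 0.3 and 64 per arm, it falls short of 80% even at zero change. Zero control change is neither necessary nor sufficient.

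A reader might also infer that the right net difference was at hand because the cited trial had a control group. The Introduction reports only the direction of that comparison and gives no control figure, so whether a usable net difference was reported cannot be told from the article.

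Finally, the Results section says data collection was complete at submission. That limits the remedy to wording but does not remove the need for it, since the results were still to be published.

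**Conclusion.** The point holds as a wrong effect input, not as an arithmetic error. The 64 reproduces exactly, but it rests on a within-arm change of 4.9 points placed where a between-arm difference belongs. The stated 80% power is therefore not established for the intervention-versus-waitlist comparison.

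The size of any shortfall cannot be fixed from the document. It depends on the control-arm change, on what the 9.865 measures, on the pre-post correlation and on how many participants are analysed. Under the normal approximation with SD 9.865, a 1-point control improvement would give 61% power with 64 analysed per arm or 73% with 84. These are illustrations, and it would be going too far to say that the trial has any particular lower power.

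The dropout allowance (64 × 1.3 = 83.2, hence 84, rather than 64/0.7, hence 92) is a separate point and forms no part of this one.

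**What to change.** Reword the Sample Size section to say that 64 analysed per group gives about 80% power for a between-group difference of about 0.50 SD (4.9/9.865), and that the 4.9 is a within-arm change in the cited study that does not itself support a difference of that size.

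If the cited trial reports an intervention-minus-control difference, use it in place of 4.9 and report the power that the fixed 84 randomised per group gives for it. In either case, name the scale and say whether 9.865 is an SD of scores or of changes. The section does neither, and a mean of 21.1 cannot be a GAD-7 score, whose stated maximum is 21.

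The cost is rewriting one paragraph and a possibly less favourable stated power. Enrolment, the outcomes and the planned analysis do not change.

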**Methods:**

A two-arm randomized controlled trial of a single-blind study will be conducted to meet the objective of this study. We aim to recruit 84 participants each for the intervention and control groups. The recruitment will be from participants who participated in the first phase of this research. The primary outcomes of this study are depressive and anxiety scores, which will be assessed using the Patient Health Questionnaire 9 and Generalized Anxiety Disorder 7, respectively. The secondary outcome includes mental health literacy of the participants, which will be assessed using the self-developed and adapted Mental Health Literacy Questionnaire. The psychoeducational intervention program consists of four sessions, which will be accessed each week. The depressive and anxiety symptoms will be compared between participants who participated in the psychoeducational program compared with the control group. Depressive and anxiety scores and mental health literacy will be assessed at week 1 and at follow-ups at week 5 and week 12, respectively.

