### Statistical Analysis

Data will be analyzed using IBM SPSS version 21.0 software. Differences between sociodemographic characteristics for the intervention and control groups will be tested using chi-square and *t* tests. A mixed between-within subjects ANOVA will be employed to compare the mean difference of the psychoeducation intervention program between the two groups at pretest, posttest (week 5), and at 2-months of follow-up (week 12). The magnitude effect size of the intervention program will be calculated using Cohen’s formula. Analyses will be conducted based on the intention-to-treat principle and for all completers.

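### The 30% dropout allowance is miscalculated: 84 per group leaves about 59 completers, not the 64 that the stated 80% power needs (92 per group would)

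*Protocol article*

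**What the plan says.** The Sample Size section of the protocol article uses the standard two-sided formula for comparing two independent means. It sets confidence at 95% and power at 80%, with an SD of 9.865. The two means entered in the formula are described as "a baseline and posttest mean score of 21.1 and 16.2, respectively, in the intervention group", a difference of 4.9 points taken from a cited study. The result before any allowance for loss is that "the calculated sample size was estimated to be 64 participants". The formula returns a number per group, and the final figure is also given per group, so 64 is per group.

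The next sentence makes the allowance: "Taking into consideration a 30% dropout rate [30], the final sample size calculated was 84 participants in each group". The abstract repeats the result as the recruitment target: "We aim to recruit 84 participants each for the intervention and control groups". The article does not show how 64 became 84 and gives no other reason for 84.

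On analysis sets, the Statistical Analysis section says: "Analyses will be conducted based on the intention-to-treat principle and for all completers".

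**The concern.** A dropout rate is a share of the people enrolled. To finish with a required number of completers, that number is divided by the share expected to remain. Multiplying it by one plus the dropout rate gives too small a figure, and the gap grows with the rate. At 30% it is no longer a matter of rounding.

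The article gives three figures: 64 needed, 30% lost, 84 enrolled. If 30% of 84 are lost, fewer than 64 remain, so the three cannot all hold. At stake is the power statement attached to the recruitment target: a reader will take it that 84 per group secures 80% power with 30% dropout, and by the plan's own calculation it does not.

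**Working it through.** **Inputs, all from the Sample Size section:** two-sided α = 0.05 (95% confidence, with Z for 1−α/2 in the formula); power 0.80; SD 9.865; difference 21.1 − 16.2 = 4.9; dropout 30%; final size 84 per group.

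**1. Reproduce the size before dropout.**

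n = 2σ²(Z₁₋α/2 + Z₁₋β)² / (μ₁ − μ₂)² = 2 × 9.865² × (1.960 + 0.842)² / 4.9² = 63.63, rounded up to 64 per group.

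This agrees with the article. A one-sided test would give 51, so the two-sided reading is the one the authors used.

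**2. Apply the dropout allowance.**

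| Method | Calculation | Per group | Completers after 30% loss |
|---|---|---|---|
| Divide by the share remaining | 64 / 0.70 = 91.4 | 92 | 92 × 0.70 = 64.4 |
| Multiply by 1.30 | 64 × 1.30 = 83.2 | 84 | 84 × 0.70 = 58.8 |

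Starting from the unrounded 63.63, division gives 90.9, so 91. Neither form of the division gives 84. That 84 came from multiplying by 1.30 is an inference from the match, because the article does not print the step. The inconsistency does not depend on it: 84 × 0.70 = 58.8 is below 64 however 84 was reached.

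**3. Shortfall in enrolment.** 92 − 84 = 8 per group; in total 184 − 168 = 16.

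**4. Dropout that 84 per group can absorb.** 1 − 64/84 = 0.238, or 23.8%.

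**5. Power with the completers that remain.** Using the plan's difference and SD, power ≈ Φ(4.9 / [9.865 × √(2/n)] − 1.960):

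| Completers per group | Normal approximation | t distribution |
|---|---|---|
| 64 | 80.2% | 79.6% |
| 59 | 77.0% | 76.3% |
| 58 | 76.3% | 75.6% |

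The normal approximation is the basis of the article's formula. On that scale, the loss at 30% dropout is 3 to 4 percentage points.

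**The case against.** No reading of the section makes 84 per group with 30% loss leave 64. The serious objections concern how much this matters.

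- **Dropout is not defined.** If the 30% refers to people who stop the programme but still complete the assessments, all 84 per group could be analysed. The same formula then gives about 90% power, before any dilution of the effect. The source cited for the rate is not at hand, so this cannot be settled. It is a weak defence: the section inflates for dropout, which makes sense only if dropouts are lost to the analysis. A completers analysis is planned as well, and intention-to-treat does not restore scores that were never collected.
- **The planned analysis is not the one in the formula.** The outcome is change from baseline, analysed by mixed ANOVA over three time points. Power for a change score depends on the correlation r between baseline and follow-up, which the article does not give. If 9.865 is the SD of a score at one time, then SD of change = 9.865 × √(2(1−r)). With 58 per group, power for one baseline-to-follow-up change is about 69% at r = 0.4, 76% at 0.5, 85% at 0.6 and 93% at 0.7. This point stands: 76 to 77% is the power under the article's own calculation, not an estimate for the planned model.
- **The 4.9-point difference is a change within one arm of another study.** Whether it suits a between-group comparison on the PHQ-9 or GAD-7 is a separate question. It does not rescue the arithmetic, but a corrected sentence must not present any power figure as unconditional.
- **The effect is small and enrolment is over.** Both are true. They limit the remedy to a correction of the text.

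**Conclusion.** The concern holds. The article's figures of 64 needed, 30% lost and 84 enrolled per group contradict one another, and nothing else in the article reconciles them. A 30% loss calls for 92 per group. At that loss, 84 leaves 58 to 59 completers and about 76 to 77% power by the normal approximation (75.6 to 76.3% with the t distribution), against the stated 80%.

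The conclusion on sample size needs only the printed figures and the ordinary meaning of a dropout rate as a share of those enrolled. The power figures also take the plan's difference, SD and two-means formula as given, and count dropouts as absent from the analysis. The error is certain but modest in size. It affects the stated power and leaves the endpoints, the tests and the type I error unchanged.

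**What to change.** Replace the sentence on dropout in the Sample Size section with one to this effect:

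> With the difference of 4.9 and SD of 9.865 assumed above, 64 completers per group are needed for 80% power. Enrolling 84 per group provides them if dropout is at most 23.8%. At the assumed 30% dropout, about 58 to 59 per group remain, and power by the same formula is about 76 to 77%. Allowing for 30% dropout would require 92 per group.

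The opening condition should stay: 92 corrects the allowance and does not by itself establish 80% power for the PHQ-9 or GAD-7. The abstract may keep 84 as the number aimed for, provided the power attached to it is the corrected one.

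The cost is one sentence and a slightly less favourable power statement. The article's Results section says data collection was complete at submission, so no further enrolment is asked for and no analysis changes.
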